### Statistical analysis

All statistical analysis will be carried out by the professionals using SPSS (v21.0) software. The participants in the statistical analysis will be unaware as well for the specific grouping content of the trial. This study will use a full analysis set (FAS) and per protocol set (PPS), and the final conclusion will be based on FAS. The full analysis set (FAS) is based on the intent to treatment (ITT). Patients who participate in randomization and receive at least one treatment will be included in the analysis. In the FAS analysis, for patients who do not complete the trial, the main indicators of the missing will be derived from the Last Observation Carried Forward (LOCF). Continuous variables will be presented as mean ± standard deviation (normally distributed data) or medians and ranges (non-normally distributed data). Frequencies and percentages will be used to count the data. All statistics will be performed by bilateral differential test, with *P* value < 0.05 considered statistically significant.

For the balance of basic values, analysis of variance or chi-square test or rank sum test will be used. For the primary and secondary outcome, the analysis of variance will be used. If confounding factors have an impact on the results, then the co-variance analysis will be used. For the safety analysis, the incidence of three groups of adverse events will be compared using a chi-square test, and the adverse events that will occur in this trial will be listed. At the same time, the paired *t* test will be used to compare the differences between the groups before and after treatment. The comparison among the three groups before and after treatment will be analyzed by variance. The rate changes before and after treatment in the three groups will be measured by chi-square test or non-parametric test.

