## Background

### Epidemiology and current management

The shoulder joint is the joint which involves the largest range of human activities. It can perform complicated work and exercise. Therefore, their significance is inevitable in daily work activities of the human being. Shoulder pain is a common disease with high morbidity in patients attending daily outpatient clinics [1–4]. The frozen shoulder is a type of shoulder disease in which the active and passive movements of the shoulder joints are significantly restricted for no apparent reasons. The study carried out by Codman [5] in 1934 pioneered the term “Frozen Shoulder.” Later, the American Academy of Shoulder and Elbow Surgeons defined the disease as “adhesive arthritis of the glenoid-humeral joint” [6]. At present, the two names such as “frozen shoulder” and “adhesive arthritis” are used worldwide. Generally, middle-aged and elderly people in their 40s and 60s are most susceptible to the frozen shoulder disease. In the normal population, occurrence of this disease is about 2 to 5%, whereas diabetic patients are more susceptible to the occurrence rate as high as 20% [7]. The frozen shoulder is mainly divided into idiopathic frozen shoulder and secondary frozen shoulder. Idiopathic frozen shoulder is considered as a diagnosis for all cases in which specific trauma, known comorbidity, or underlying etiology cannot be identified. The clinical characteristics can be defined with shoulder pain and mechanical restriction in all planes of movement of the glenohumeral joint [8]. It is considered to be a self-limiting disease that can resolve within 1 to 3 years. However, shoulder pain and limited mobility in some people may take years and some carry it for life-long [9]. Various studies and researches have shown that 20 to 50% of patients may continue to develop persistent symptoms [10]. The previous studies were carried out with continuous follow-up of 41 frozen shoulder patients for the period of 5–10 years; however, recovery was observed in only 39% of the patients. The long-term pain and limited mobility of most patients seriously affected their normal daily life [11]. It requires a management plan differing from other shoulder conditions [12]. Efforts to find out effective therapies to relieve pain and increase the range of motion are essential to improve the quality life of patients suffering from frozen shoulder.

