## Outcomes

The following outcomes will be assessed by independent outcome assessors. These assessors will be trained before participating in this trial and unaware of the group assignments. The outcome assessments will be performed at four time points including at the baseline, at the end of the stuck-moving needle acupuncture treatments, in the 4-week follow-up period, and at the end of the follow-up period.

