### Main outcome indicators

The primary evaluation index in the trial will be the change involved in the scores on the Visual Analogue Scale (VAS) and measurement of range of joint motion (ROM) from the baseline period through the 12 weeks of the follow-up period.

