The setting of control group also plays an important role in the efficacy evaluation. It is the basis of accurate evaluation of curative effect. According to the WHO published guidelines for clinical research in acupuncture and moxibustion requirements for the establishment of control groups in clinical studies of acupuncture and moxibustion, we set up two control groups. Exercise programs are the basic treatment and also a control group. The common acupuncture group is a positive control group, and the stuck-moving needle was used to acupuncture MTrp as the treatment group, to verify the effectiveness of treatment group.

The selection of appropriate outcome is crucial when designing clinical trials. A review of shoulder pain trials found that trialists reported pain in 87%, function in 72%, range of motion in 67%, adverse events in 27%, patient-reported treatment success in 24%, strength in 18%, and health-related quality of life in 18% [37]. Therefore, we choose primary outcomes including a measure of pain (VAS) and range of motion (ROM), whereas secondary outcome included a measure of pain (PTT and PPT), function (OSS), health-related quality of life (SF-36), patient satisfaction evaluation, and adverse events. The measurement time was from baseline through the 12-week follow-up period.

However, this study also has its limitation. First, the implementation of the blind method is difficult due to the nature of acupuncture, and the masking of acupuncturists is quite difficult to achieve. However, the statistician will be masked. Second, the follow-up time is too short, probably due to the current status of research funding and research time, and patients were followed up for a period of 12 weeks after the end of treatment in this study. Follow-up was performed at week 4 and week 12. Frozen shoulder is a chronic degenerative osteoarthropathy with a long course and the high possibility of recurrence. Therefore, for the future trial design, the follow-up time should be appropriately extended and comprehensive evaluation should be carried out with the long-term treatment effect for frozen shoulder by the stagnant acupuncture method. Nonetheless, the trials carried out in this study and subsequent results will provide more reliable evidence for clinical treatment of FS.

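### Carrying the last observation forward in the deciding analysis scores patients lost during treatment as zero change and lets unequal loss between arms appear as a treatment effect

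*Protocol article*

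**What the plan says.** All references are to the protocol article.

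- **Missing data (Statistical analysis).** In the full analysis set (FAS), for patients who do not complete the trial, "the main indicators of the missing will be derived from the Last Observation Carried Forward (LOCF").
- **Which analysis decides (same section).** "the final conclusion will be based on FAS". The only other analysis set named is the per-protocol set.
- **Who is in the FAS (same section).** "Patients who participate in randomization and receive at least one treatment will be included in the analysis". No post-baseline value is required.
- **Visits (Outcomes).** "The outcome assessments will be performed at four time points including at the baseline, at the end of the stuck-moving needle acupuncture treatments". The other two are at 4 weeks of follow-up and at the end of follow-up.
- **Primary endpoint (Main outcome indicators).** Change in VAS and "measurement of range of joint motion (ROM) from the baseline period through the 12 weeks of the follow-up period".
- **Course of the disease.** Epidemiology and current management: "It is considered to be a self-limiting disease that can resolve within 1 to 3 years". Discussion: "Frozen shoulder is a chronic degenerative osteoarthropathy with a long course and the high possibility of recurrence". The Discussion also mentions some tendency to heal unaided.
- **A second entry rule (Patient dropouts).** A subject who has received half of the treatment is to be counted in the efficacy analysis. This differs from the one-treatment rule of the FAS.

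**The concern.** LOCF treats a patient's outcome as fixed from the last visit attended. Here that happens in two ways.

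1. **Loss during the three treatment weeks.** Only the baseline value exists, so the carried change is exactly zero whatever happened to the patient.
2. **Loss after the end-of-treatment visit.** The end-of-treatment value, or the 4-week value if that visit was attended, stands in for week 12. The protocol describes a condition that can resolve on its own and can recur, so constancy is an assumption that its own background does not support.

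If loss differs between arms, either route turns the difference in loss into a difference in VAS or ROM. Unequal loss is plausible. Patients cannot be masked to the needling (Rationale for the trial design). The stuck-moving needle is described as the stronger stimulus, and common acupuncture as less painful (Rationale for the use of intervention). The exercise arm consists of people who agreed to receive acupuncture (inclusion criteria) and get none. At stake is the comparison of the two needling methods, which is the trial's stated purpose and has the smallest planned difference.

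**Working it through.** **Inputs (Sample size estimation).** Planned VAS changes: stuck-moving needle (A) 5.2, SD 1.06; common acupuncture (B) 4.7, SD 1; exercise (C) 3.5, SD 1. There are 36 patients per arm. These are before-to-after-treatment changes, used here as stand-ins for the 12-week change.

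**The plan's loss allowance.** 30 × 1.2 = 36 and 3 × 36 = 108, as stated. This corresponds to losing 6 of 36 (16.7%) per arm over the whole trial. The protocol gives no split by time or arm. The stated power of 0.931 at 30 per group does not reproduce (the one-way F-test gives more than 0.999), but that is a separate matter and nothing below uses it.

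**Early loss, formula.** If a fraction d of an arm is lost before the end-of-treatment visit and carried at zero:

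- mean = μ(1 − d)
- variance = (1 − d)σ² + d(1 − d)μ²

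**Unequal early loss, A only (assumed).**

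| Early losses in A (of 36) | Mean change in A | B, no loss | A − B |
|---|---|---|---|
| 0 | 5.20 | 4.70 | +0.50 |
| 3 | 5.2 × 33/36 = 4.77 | 4.70 | +0.07 |
| 4 | 5.2 × 32/36 = 4.62 | 4.70 | −0.08 |
| 6 | 5.2 × 30/36 = 4.33 | 4.70 | −0.37 |

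The planned advantage is gone once losses exceed 36 × 0.5/5.2 = 3.5, that is, at four patients. With early loss of 20/10/10% in A/B/C, A − B is 4.16 − 4.23 = −0.07. With 10/20/10% it is 4.68 − 3.76 = +0.92. The bias can favour either arm.

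**Equal early loss (assumed), 6 of 36 in every arm.** Means are 5.2 × 5/6 = 4.33, 4.7 × 5/6 = 3.92 and 3.5 × 5/6 = 2.92. A − B falls from 0.50 to 0.42 and A − C from 1.70 to 1.42. The pooled SD rises to about 1.93. At 36 per arm, power of the overall F-test falls from above 0.999 to about 0.82, and power for A against B falls from 0.52–0.56 to about 0.15.

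**Effect on the standard error.** With 4 of 36 zeros in A, the SD is √(0.889 × 1.06² + 0.0988 × 5.2²) = √(1.00 + 2.67) = 1.92. The standard error is 1.92/√36 = 0.32, against 1.06/√32 = 0.19 for the 32 observed patients.

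**False-positive rate (simulation).** 20,000 trials, 36 per arm, true change 4.7 and SD 1 in all arms. The F-test rejects in about 5% of trials when early loss is equal, and in about 17–18% when one arm loses 20% and the others 10%. The excess comes from bias.

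**Late loss.** The arm mean is wrong by d × r, where r is the mean change after the last attended visit. The protocol gives no r. If d is 10–20% and r is 0.5–2 VAS points, the shift is 0.05–0.40 points. Both ranges are assumptions.

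No planning figure exists for ROM, so the same effect there cannot be sized.

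**The case against.** The strongest reply is that the harm depends on a loss pattern the protocol does not document. The allowance of six per arm is equal across arms and covers the whole trial, so it does not support an imbalance of four patients within three weeks. Retention measures are planned: free acupuncture, a subject manual and text messages. If the half-of-treatment rule governs, many baseline-only patients would never enter the analysis. All of this limits the size, not the mechanism. Even under that rule, a patient lost between about the fifth of nine sessions and the end-of-treatment visit still carries baseline. The rule also conflicts with the FAS definition.

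Three stronger readings are tempting, and the document does not support them.

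- **LOCF makes the standard errors too small.** A reader might infer this because imputed values count as data. It can hold for later carried values, but zeros among changes near 5 inflate the SD, as shown above.
- **The condition relapses within the 12 weeks.** The text says it can resolve over 1 to 3 years and may recur, and it raises recurrence as a reason for longer follow-up in future trials. It gives no rate of change between the end of treatment and week 12.
- **Every late drop-out carries the value taken straight after needling.** A patient who attends the 4-week visit carries that value, and the protocol does not say that the end-of-treatment assessment follows immediately after needling.

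An unseen analysis plan could add sensitivity analyses. It would not change the fact that the protocol fixes LOCF for the deciding analysis, and the per-protocol set does not test the missing-data assumption.

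**Conclusion.** The concern holds as a stated rule that is fixed badly. Given the visit schedule and the FAS definition, zero change for patients lost during treatment follows directly and needs no assumption about the disease. Entering an end-of-treatment or 4-week value as the 12-week result is also certain to happen for later losses, but the size and direction of that error are unknown.

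The figures are scenarios, resting on assumed numbers and timing of losses and on planning changes used as 12-week changes. Within them, a four-patient early imbalance is enough to remove the planned 0.5-point advantage of A over B. Equal early loss at the full allowance leaves 0.42 with nearly double the SD. The contrasts with exercise are larger and less easily overturned. The bias can go either way. Differential loss is plausible from the design but is not shown by the document.

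**What to change.** 1. **Primary method.** Replace LOCF by a mixed model for repeated measures over the existing visits, with group, visit, group × visit, centre and an unstructured covariance. Take the group contrasts at 12 weeks of follow-up. The MIXED procedure in the named SPSS can fit this.
2. **Baseline-only patients.** A model of post-baseline values with baseline as covariate would drop them, although the FAS includes them. Either model baseline as one of the responses with a common mean across arms (group effects entering only after baseline) or use multiple imputation.
3. **Sensitivity.** Add a delta-adjusted analysis for data not missing at random. Patients with only a baseline value carry little information about week 12 under any method, so this is the step that tests their influence. Keep LOCF at most as a further sensitivity analysis.
4. **Analysis set.** Reconcile the one-treatment rule in Statistical analysis with the half-of-treatment rule in Patient dropouts, so that one rule defines who enters the deciding analysis.

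The cost is revised wording and a little more programming, with no new data. The primary analysis would rest on a missing-at-random assumption, which the delta-adjusted analysis is there to test. The change should be made before the group codes are opened.

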### Participants

#### Participants criteria

The inclusion criteria for patient selection are as follows:
The age shoulder between 40 and 70 years old.Shoulder pain is self-reported, whereas the pain range extends from the medial side of the shoulder to the biceps area or the outside of the deltoid muscle. The VAS score is between 7 and 8 points.The onset of pain lasts for at least 3 months.The stiff shoulder pain is a spontaneous attack, and the shoulder lifting or external rotation function is lost by 50%, and the OSS score is between 50 and 60 points.Being able to actively cooperate with the doctor and sign the consent form to voluntarily receive acupuncture treatment.

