### Random and allocation of hidden methods

The number of observed subjects will be allocated based on the actual situation of each center. The subjects in each center will be divided into three groups by random number table method and serial numbers will be allocated (such as 1, 2, 3, ..., *N*, this serial number is the ID of the subjects who will participate in the study). Then starting from any number on the random number table, the number of subjects will be selected in the sub-center. SAS (v9.4) software will be used to generate the random numbers corresponding to the above serial number. The number will be divided by 3; if the remainder is 0, then the subject will be included in the acupuncture myofascial trigger points’ group. If the remainder is 1, subject will be included in the common acupuncture group, and if the remainder is 2, then the subject will be included in the functional exercise group. According to the result of the grouping, the random card will be made, sealed in an opaque envelope, and will be kept by a responsible person. In the clinical implementation, the order in which the qualified subjects will be included in the test is in one-to-one correspondence with the sequence number on the envelope, and the envelopes will be opened and grouped according to the prompts on the random card.

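### The switch from ANOVA to covariance analysis depends on an undefined effect on the results, so the model for the primary outcomes is settled only after outcome data are seen

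*Protocol article*

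**What the plan says.** All of the analysis rules are in the Statistical analysis section of the protocol article.

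- Default model: "For the primary and secondary outcome, the analysis of variance will be used".
- Exception: "If confounding factors have an impact on the results, then the co-variance analysis will be used". The section does not say which factors count, how an impact is judged, or which result then decides.
- Baseline: "For the balance of basic values, analysis of variance or chi-square test or rank sum test will be used". No consequence for the outcome model is attached to these tests.
- Paired t test: it "will be used to compare the differences between the groups before and after treatment". The next sentence gives the three-group before-after comparison to ANOVA.

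Two design facts bear on this. Main outcome indicators defines the primary outcomes as change from baseline in VAS and ROM. The randomisation section states that "The subjects in each center will be divided into three groups by random number table method", and Study design names three centres. Centre does not appear in any stated model.

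**The concern.** Whether a covariate affects the results is a property of the outcome analysis. A rule triggered by that effect can be applied only after both the unadjusted and the adjusted results are available, or at least after covariate-outcome associations have been examined. With no criterion written down, two competent analysts could follow the protocol and report different primary P values. That leaves room for the more favourable one to be reported, and it gives a reader no way to tell whether it was.

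The conditional rule also means that baseline and centre, both already recorded, may go unused as covariates. For outcomes with wide baseline spread that gives away precision.

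The paired t test is a smaller matter. As worded, a test that compares before with after inside one arm is described as comparing groups. Background calls the condition self-limiting, so improvement within an arm is not evidence for one treatment over another.

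**Working it through.** The plan gives no figure of its own on this point, so there is none to reproduce. Its sample size calculation is not at issue here.

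**Inputs from the protocol article.** 36 patients per arm, three arms, two-sided 5% level; SD of VAS change about 1 (Sample size estimation); entry rule "The VAS score is between 7 and 8 points" (Participants criteria); allocation by remainder after division by 3 within centre, with no blocks described (randomisation section).

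**Assumptions not in the documents.** Baseline-to-final correlation rho of 0.3, 0.5 or 0.7; for VAS, a uniform baseline over 7-8 and a baseline-to-final slope of 1, 0.5 or 0.

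**1. Error rate if the smaller of two P values is reported, equal baseline and final variances.** Simulation with no treatment effect, 6,000 runs, change-score ANOVA against ANCOVA:
- rho 0.3: 8.1%
- rho 0.5: 7.2%
- rho 0.7: 7.1%

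Either test alone rejects in about 5%. The simulation standard error is about √(0.08 × 0.92 / 6,000) = 0.35 percentage points, and repeat runs agree within it.

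**2. The same rule for VAS.** A uniform baseline over one point has SD 1/√12 = 0.289. With change SD 1, repeated runs give about 5.4% to 6.7% across slopes 1 to 0. The rate is lower because baseline explains so little of the change that the two tests nearly coincide.

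**3. A different reading of the trigger: adjust only if the baseline test is significant.** With the final score analysed (4,000 runs; adjusted model with baseline and centre), rejection is 4.4%, 4.1% and 3.5% at rho 0.3, 0.5 and 0.7. There is no inflation, and a check with change scores also shows none. A fixed ANCOVA with baseline and centre gives 4.8% to 5.1%.

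**4. Precision.** With equal variances scaled to 1, the change score has variance 2(1 − rho) and ANCOVA has residual variance 1 − rho². The ratio is (1 − rho²) / [2(1 − rho)] = (1 + rho)/2:
- rho 0.3: 0.65, a 35% reduction
- rho 0.5: 0.75, a 25% reduction
- rho 0.7: 0.85, a 15% reduction

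For VAS, the share of change variance explained by baseline is (1 − slope)² × var(baseline) / var(change). With variance 1/12 this is 0.25 × 0.083 = 2% at slope 0.5 and 8% at slope 0. The largest possible SD on a 7-8 range is 0.5, so the ceiling at slope 0 is 0.25 / 1 = 25%.

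**5. Centre.** Allocation is described as simple randomisation within each centre. Leaving centre out of the model therefore does not by itself distort type I error. The documents give no between-centre variance, so the gain from including it cannot be sized.

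**The case against.** The best defence is that the sentence is loose English for a familiar practice: test baseline balance, then adjust for what is imbalanced. The balance tests come just before it, and under that rule the error rate does not rise. The Blind method and Statistical analysis sections also keep analysts unaware of group identity, which limits steering towards a favoured arm. A condensed article may leave the covariate list to a fuller document.

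Part of this stands. The imbalance reading is possible, and blinding does lessen deliberate selection. But the text ties the switch to the results, not to balance, and a blinded analyst can still see which model gives the smaller P value. This is also not an omission: the article states a rule, and a later plan that fixed the model would have to override it.

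Four stronger readings might be inferred, and the documents do not support them.
- That baseline is ignored. It is not: change from baseline is the primary outcome.
- That the error rate will be 7-8%. That figure needs selection of the smaller P value and equal variances, and it does not describe VAS.
- That omitting centre invalidates the comparison. Without blocking, it costs only efficiency.
- That arms will be compared by paired t test. The following sentence assigns that comparison to ANOVA, so a within-group test is the likely meaning.

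**Conclusion.** The concern holds in a limited form. The protocol fixes an outcome-dependent, undefined rule for choosing the model for its primary outcomes, and baseline is not a prespecified covariate. The inflation in type I error is conditional: about 7-8% under worst-case selection with equal variances and correlation 0.3-0.7, which is relevant to ROM; about 5.4-6.7% for VAS; none if the trigger is baseline imbalance alone. The lost precision is 15% to 35% of variance under the same equal-variance assumption, mainly for ROM, PPT/PTT and SF-36. For VAS it is about 2% to 8% with a uniform baseline and slope 0.5 to 0, so adjustment should not be expected to change the VAS comparisons much. The missing centre term is an efficiency point of unknown size. The paired t test sentence is a wording fault. The change is worth making because it is nearly free and removes the ambiguity, not because the trial's conclusions are shown to be unsafe.

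**What to change.** Replace the conditional sentence with one prespecified analysis: each continuous outcome is analysed by a linear model with treatment group, the baseline value of that outcome and centre as fixed terms, whatever balance is observed. Report adjusted A-B, A-C and B-C differences with 95% confidence intervals. Keep the unadjusted ANOVA as a labelled sensitivity analysis, and state that baseline significance tests do not decide the model.

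Reword the paired t test sentence so that it describes before-after change within each arm and is not offered as evidence of a difference between arms.

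The cost is analysis wording and three model degrees of freedom (one for baseline, two for three centres). No new data are needed, since baseline and centre are already recorded.
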